# Study protocol of the multi-centre, randomised controlled trial of the Frankfurt Early Intervention Programme A-FFIP versus early intervention as usual for toddlers and preschool children with Autism Spectrum Disorder (A-FFIP study)

**DOI:** 10.1186/s13063-019-3881-7

**Published:** 2020-02-24

**Keywords:** Autism spectrum disorder, NDBI, ASD-specific, Early intervention, A-FFIP, Randomised trial

## Abstract

**Background:**

Naturalistic developmental behavioural interventions (NDBI) have been shown to improve autism-specific symptoms in young children with Autism Spectrum Disorder (ASD). NDBI approaches, such as the ASD-specific Frankfurt Early Intervention Programme for ASD (A-FFIP), are based on ASD-specific developmental and learning aspects. A-FFIP is a low-intensity intervention which can easily be implemented in the local health care/social welfare system. The aim of the present study is to establish 1-year efficacy of the manualised early intervention programme A-FFIP in toddlers and preschool children with ASD. It is hypothesised that A-FFIP will result in improved ASD-specific symptoms compared to early intervention as usual (EIAU). Child- and family-specific secondary outcomes, as well as moderators and mediators of outcome, will be explored.

**Methods/design:**

A prospective, multi-centre, parallel-group, randomised controlled, phase-III trial comparing A-FFIP versus EIAU. A total of 134 children (A-FFIP: 67, EIAU: 67) aged 24–66 months at baseline assessment meeting the criteria for ASD (*DSM-5*) will be included. The primary outcome is the absolute change of the total score of the Brief Observation of Social Communication Change (BOSCC-AT) between baseline (T2) and 1-year follow-up (T6). The treatment effect will be tested, adjusted for relevant covariates applying a mixed model for repeated measures. Secondary outcomes are BOSCC social communication and repetitive-behaviour scores, single ASD symptoms, language, cognition, psychopathology, parental well-being and family quality of life. Predictors, moderators and mediating mechanisms will be explored.

**Discussion:**

If efficacy of the manualised A-FFIP early intervention is established, the current study has the potential to change clinical practice strongly towards the implementation of a low-intensity, evidence-based, natural early intervention in ASD. Early intervention in ASD requires specialist training, which subsequently needs to be developed or included into current training curricula.

**Trial registration:**

German Registry for Clinical Trials (Deutscher Register Klinischer Studien, DRKS); ID: 00016330. Retrospectively registered on 4 January 2019. URL: https://www.drks.de/drks_web/navigate.do?navigationId=trial.HTML&TRIAL_ID=DRKS00016330.

## Background

Autism spectrum disorder (ASD; *Diagnostic and Statistical Manual of Mental Disorders, version 5 (DSM-*5)) is a chronic, pervasive, developmental disorder with a prevalence of ~ 1%, a male: female ratio of ~ 4:1, and a high burden of disease for the affected individuals and their families [1]. Lifetime health economic costs have been estimated for the UK and the US at US$1.4–2.2 million [2]. To date, just 5–10% of adult ASD individuals are living independently in Europe [3]. It is likely, that effective early intervention will decrease long-term costs and improve outcome [4].

Toddlers and preschool-aged children with ASD show severe impairments in many developmental areas, such as visuo-motor abilities, attentional control, joint attention, imitation, social orientation and motivation, social cognition, play, abstract and concept formation, communication and language, emotion regulation and executive function [5–7]. These ultimately result in chronically impaired language, social communication and interaction with peers and adults, which are predictors of adult outcome in ASD [8]. To improve long-term outcomes, thus, developmentally based early intervention needs to be studied for efficacy on the child’s core ASD symptoms as well as on other important developmental areas such as language, cognition and behaviour.

Early intervention in ASD differs with regard to the underlying developmental theory, treatment targets, therapeutic methods, involvement of parents, and intervention intensity. Recent comprehensive systematic reviews [9, 10] agree that the evidence base of any treatment is at maximum moderate, and improvement of core autistic symptoms has rarely been studied. Many of the studied early intervention programmes for toddlers and preschool-aged children are either complex, targeting a broad range of areas with high intensity (> 10, up to 40 h/week work with therapists) [11, 12], or are highly specific with low intensity, targeting core developmental aspects, such as joint attention and symbolic play [13], parent-child interaction [14] or language abilities [15].

High-intensity, therapist-centred, discrete trial trainings (DTT) were studied first [12]. The studies were mostly of low quality, and showed medium to large effects on measured Intelligence Quotient (IQ), but no improvement of core autistic symptoms or behaviour problems. Over time, this approach has been developed further into various new ‘Naturalistic Developmental Behavioural Interventions’, so called NDBIs, in which the behavioural basis has extended by more natural and developmentally relevant components. NDBIs are characterised by naturalistic settings, shared control between child/therapist, natural contingencies, and a variety of behavioural strategies to teach developmentally appropriate, prerequisite skills [16]. In addition, they are including results of recent developmental psychological findings on early development in autism to teach and practise core basic skills, which are impaired in many children with ASD. NDBIs have been shown to increase the child’s motivation to learn, and focus on the integration of knowledge and skills as well as generalisation across different developmental areas [16]. A growing evidence base for NDBIs has been generated, and a recent meta-analysis, including clinical as well as randomised controlled trials (RCTs), reported large effects on improvement of social engagement, medium gains in cognitive development and reduction of core ASD symptoms [17].

One- and 2-year efficacy, especially on improvement of cognitive skills, has been shown by a randomised controlled trial (RCT) on the Early Start Denver Model (ESDM), which is a high-intensity, complex early intervention programme based on a combination of DTT and NDBI methods, the latter focussing on parental synchrony and reciprocity [11]. Again, no improvement of ASD-specific symptoms (Autism Diagnostic Observation Schedule (ADOS) severity score) was observed after 1 and 2 years of intervention compared to treatment as usual with a similar intensity. In a 6-year follow-up study (81% of the original sample), however, long-term improvement of ASD-specific symptoms was reported [18].

Several low-intensity NDBI programmes targeting specific ASD-relevant developmental impairments, such as joint engagement, joint attention, play, imitation, parent-child interaction and language abilities were studied by various RCTs [13–15, 19–22]. All the interventions resulted in clear improvements of the trained abilities, but more distant outcomes often were not assessed. In a secondary analysis, one study on parent-child interaction training showed a medium effect on core ASD symptoms after 13 months, which was maintained at 5-year follow up [23].

No effective, low-intensity, complex NDBI targeting a broad range of developmental areas is available to date. Here, we propose to study a new, complex, manualised, comprehensive and individualised, low-intensity NDBI programme, A-FFIP ([5], more details are provided under the ‘Treatment principles’ section).

A-FFIP usually is provided over a period of 1–3 years before starting school-based education. Pre-post pilot data showed medium effects after 1 year on ASD-specific symptoms [24], language and cognition [25, 26]. Data from a matched, observer-blind case-control study (2 x *N* = 20) confirmed a medium effect size (*ƞ*^2^ = .087; 95% CI .00–.16) of ASD-specific improvement measured by the ADOS severity score compared to early intervention as usual (EIAU) [27].

In addition to establishing efficacy with regard to different outcomes, some early intervention studies on parent trainings explored possible treatment mechanisms (‘why?’). Effectively trained parental behaviour towards the child (parental synchrony [28], parental responsiveness [29], parental mirrored pacing [30]) resulted in increased child’s initiations and joint engagement during parent-child interactive play in three studies [28–30] and ultimately improved ASD-specific symptoms in two studies [28, 29]. Treatment mechanisms of therapist-mediated early intervention have not yet been studied. Possible advantages of therapist- compared to parent-mediated intervention are a faster and more specific gain in pivotal skills by targeted exercises, which, in turn, may influence parental behaviours positively. In addition, mechanisms which go beyond social interaction and social motivation have not been studied, despite the clear notion of additional impairments in ASD going beyond the ‘social-first’ hypothesis in ASD [5, 7].

Given the high variability in outcomes in all early intervention trials, predictors (main effect) and moderators (time × treatment interaction) of treatment outcome (‘for whom’) also need to be studied to be able to individually select specific interventions in the future [31]. A recent review has summarised the following possible predictors and moderators of intervention outcome in ASD: child’s pre-treatment cognitive, adaptive, language, joint-attention and play abilities, and maternal educational level [32]. A longitudinal study on developmental trajectories in preschool-aged children indicated sex and age at diagnosis as additional possible moderators [33].

Recent innovative eye-tracking and body-movement analysis studies aim at objectively measuring sensory perception [34], visual orientating preferences [35, 36] and imitation abilities [37]. Perception, attention, and imitation impairments are likely to underlie core autistic symptoms [7]. In preschool children with ASD, attenuated pupil dilatation to emotion-expressing faces was associated with autistic symptoms [38]. Attenuated visual orientating to social cues (i.e. social attention) is a well-replicated finding in children with ASD [39]. Visual orientating preference for biological motion in preschoolers with ASD predicted symptom reduction after 1 year [36]. In a functional magnetic resonance imaging (fMRI) study with 6-year-old children, pre-treatment levels of neural activity in response to biological versus scrambled motion in four distinct brain regions predicted intervention outcome of a 16-week NDBI (7 h/week) [40]. Eye-tracking and body-movement analysis are feasible and largely tolerated by preschool children with ASD [41]. However, no study applied eye-tracking or objective movement parameters as predictors of outcome in an intervention study.

Limitations of previous studies on complex and targeted NDBI approaches are (1) the lack of a change-sensitive outcome measure capturing core autistic symptoms in a blinded fashion [42], (2) the focus on techniques instead of individualised treatment targets [6, 43] and (3) the lack of complex, low-intensity programmes, which are cost-effective and can be implemented in the community setting [6].

To overcome these limitations, (1) the Brief Observation of Social Communication Change (BOSCC-AT) is used as primary outcome in the current study. This new, ASD-specific, video-based coding system can be obtained by blinded raters and has already shown sensitivity to change in previous studies [24, 44]; (2) A-FFIP is an individualised approach targeting six basic key domains and, additionally, five specific areas of development which are impaired in ASD. Especially training the basic key domains in a developmentally appropriate way is expected to strongly influence child-initiated social learning processes [6]; (3) A-FFIP is a complex, manualised, comprehensive NDBI programme which was conceptualised as a low-intensity approach funded by the German social welfare and health care system within a restricted frame of 2 h/week.

Given the evidence shown above, it is to be expected that A-FFIP, as a complex, low-intensity, manualised, early intervention programme targeting a broad range of ASD-specific, individualised treatment goals and involving parents in the intervention, will result in clinically relevant improvement of ASD-specific behaviour, language and cognition after 1 year.

## Methods/design

### Aims

The primary objective is to establish 1-year efficacy of the A-FFIP on change in ASD-specific symptoms, assessed by a standardised interaction scene of the child with an unknown adult, which is coded in a blinded fashion.

The secondary objectives are (1) To assess A-FFIP effects on child’s cognition, language and behaviour; on parent’s competences, anxiety, depression and stress, and family quality of life; (2) To study child’s and parents’ characteristics as predictors and moderators of outcome; and (3) To explore treatment mechanisms (mediators) related to parents’ and child’s competences and objectively measured behaviour.

### Design

The trial is designed as a confirmatory, phase-III, prospective, randomised, multi-centre, controlled, parallel-group study with two treatment arms and six measurement time points. The trial time flow is shown in Fig. 1.

**Fig. 1 Fig1:**
[figure not shown]
Schedule of assessments. Key: ADI-R Autism Diagnostic Interview - Revised, ADOS-2 Autism Diagnostic Observation Schedule, BOSCC Brief Observation of Social Communication Change, SRS-16 Social Responsiveness Scale – short version, RBS-R Repetitive Behavior Scale – Revised, CBCL 1 ½-5 Child Behavior Checklist 1 ½-5, C-TRF 1 ½-5, BRIEF-P Behavior Rating Inventory of Executive Function-Preschool version, PSOC Parent sense of competence scale, DASS-21 Depression Anxiety and Stress Scale – short form, FQOLS Family quality of Life Survey, ESCS Early Social Communication Scale, DCMA Dyadic Communication Measure for Autism, Bayley-III Bayley Scales of Infant and Toddler Development 3rd Edition, PATCS Parent Adherence to treatment and Competence Scale

### Setting

The study will take place in a clinical setting at four German study centres which provide a special outpatient service for individuals with ASD (University-based Departments of Child and Adolescent Psychiatry, Psychosomatics, and Psychotherapy at Augsburg, Dresden, Frankfurt and Würzburg). The sponsor is the Goethe University Frankfurt (GU), and the principal investigator is [name]. [name], University Hospital Frankfurt at GU. The study-related diagnostic tests for all children (A-FFIP and EIAU) are performed at the four study centres, and are coded in a blinded fashion by independent individuals who are not involved in any intervention. A-FFIP is delivered by two therapists/child at the four study centres, who are not involved in any study-related diagnostic procedures. EIAU is delivered in any local setting outside the four study sites.

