#### Setting

Sessions are provided in an outpatient setting at the respective study centre. All treatment rooms are furnished in a standardised way, with standardised and well-arranged play material, ensuring a structured environment providing orientation and a minimum of distraction.

The intervention comprises 2 h of intervention/week with two therapists working with the child. The two-therapist concept is an essential A-FFIP component. While the main therapist interacts with the child, the co-therapist acts as a shadow and prompts the child individually and in a situation-specific way, during the learning of new abilities, and only if necessary. This concept is believed to support the natural learning of the child, because the child will learn the specific skill or task faster, and the interaction with the main interaction partner (therapist/parent) is independent from any prompting efforts. If the child is very advanced and shows interest in social interaction with peers, two therapists will work with two equally advanced children. At least one parent is participating in a minimum of every fifth therapy session for psychoeducation and exercises with their individual child, with the aim of learning to use effective strategies for practising at home. Parents are asked to practise established skills at home in many naturally occurring situations; these tasks are determined by the therapist and the implementation is discussed regularly with the parents. To ensure compliance by supporting parents without increasing pressure, no specific amount of practising hours or situations is expected. Parental adherence and competence is assessed by a weekly questionnaire (PATCS, see section ‘Mediating mechanisms’).

If the child already attends kindergarten, one therapist visits the child’s kindergarten teachers, and (if existing) the personal assistant three times a year for individualised psychoeducation with the aim to support generalisation of the child’s acquired skills at kindergarten. The first appointment is organised directly at the beginning of the intervention.

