### Statistical analysis

#### Sample size calculation

Sample size calculation refers to the primary outcome measure absolute change of BOSCC-AT between baseline (T2) and 1-year follow-up (T6). An age- and DQ-matched, but not randomised, observer-blind, case-control study of 2 x *N* = 20 children with ASD aged 3.2–7.9 years and an IQ/DQ of 37–134 at the start of intervention resulted in an A-FFIP 1-year effect size of 0.61 for the ADOS-severity score [27]. In a pre-post sample (*N* = 21) aged 3.8–5.8 years with a lower IQ/DQ 37–108, the 1-year pre-post effect size of the BOSCC-AT was 0.63 [24]. ADOS items are the basis for the ADOS-severity score and the BOSCC [48]. The BOSCC shows a higher number of items coded on a 6-point scale compared to the 2-point scale of the ADOS, resulting in higher variability capturing more subtle changes (range BOSCC-AT 0–60 versus range ADOS 1–10). For the BOSCC-AT, a more moderate, clinically meaningful, effect size of 0.55 is expected. With a significant level of *α* = 5% (two-sided) and a power of 1 − *β* = 80%, a sample size of 106 (2 × 53) is required to detect an effect size of 0.55 with the two-sample *t* test (ADDPLAN, version 6.1.1). Considering a drop-out rate of 20%, 134 (2 × 67) patients will be randomised to the treatment groups. It can be expected that including covariates in the confirmatory analysis will increase power compared to the *t* test.

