The analysis of mediators will allow an exploratory therapy process analysis. Child-specific as well as parent- and therapist-specific characteristics will be explored as mediators, such as the child’s learning curve on essential abilities as joint attention. Therapist fidelity is regularly assessed which allows us to specifically elicit the role of the therapist-related competencies on intervention outcome. Parental treatment adherence and competence are assessed by a weekly questionnaire (PATCS) filled in by the parents, on their self-rated ability to implement the learned strategies in their daily routine. A-FFIP is conceptualised as a low-intensity, therapist-delivered programme, in which parents are regularly supported to encourage the generalisation of new, individually meaningful and developmentally appropriate skills in daily, natural routines. The extent of parental involvement is adjusted to the individual’s familiar needs and resources. In addition, child-specific psychoeducation is provided for kindergarten teachers. Parents and kindergarten teachers are not expected to do particular exercises with the child. Future studies might focus on more objective fidelity measures of the parental implementation of intervention methods and targets at home. In the current study, the parent rating questionnaire will provide data on the parent’s sense of satisfaction, competence and intensity using A-FFIP strategies at home. This information will again be explored as a possible mediator of therapy outcome.

If efficacy is shown, additional expected positive effects by the trial will be: (1) Improvement of care in underserved areas in Germany (such as Bavaria, Saxony); (2) Alerting many different professionals working in early intervention in ASD to effective methods and (3) Establishing an effective training and supervision method provided to professionals to achieve high treatment fidelity of evidence-based early intervention. Thus, the current study may change clinical practice strongly towards the implementation of evidence-based early intervention methods in ASD in Germany. Because A-FFIP is delivered through two therapists for a 2-h/week intervention it may also be applicable in other areas with comparable public health systems. Therefore, the study results should be of great impact for many ASD underserved regions.

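### Therapists serve only the A-FFIP arm, but neither the primary MMRM nor the sample size allows for therapist clustering in that arm

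*Protocol article*

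**What the plan says.** The first Setting section of the protocol article (under Methods/design) says that "A-FFIP is delivered by two therapists/child at the four study centres" and that EIAU takes place in local services outside those centres. The Setting section under the intervention adds that, for very advanced children interested in peers, "two therapists will work with two equally advanced children".

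Under Sample size calculation, "a sample size of 106 (2 × 53) is required to detect an effect size of 0.55" with a two-sample t test at 5% two-sided and 80% power. Then: "Considering a drop-out rate of 20%, 134 (2 × 67) patients will be randomised to the treatment groups". No ICC, caseload or design effect appears. The section expects covariates to raise power above that of the t test but does not say by how much.

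Statistical methods lists the confirmatory MMRM: fixed effects for baseline BOSCC-AT, age, treatment, time and treatment by time, with centre as a random effect. Correlation between a child's repeated measurements is modelled. Therapist is not in the list.

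The Discussion says that the fidelity ratings make it possible to "specifically elicit the role of the therapist-related competencies on intervention outcome", as part of an exploratory process analysis.

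**The concern.** Children treated by the same therapists may have more similar outcomes than children treated by different ones. Here that similarity can arise through study therapists in the A-FFIP arm only, a partially nested design. Any such variation enters the A-FFIP mean and hence the treatment difference. A centre intercept shared by both arms shifts A-FFIP and EIAU children together, so it cannot represent it.

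Two things are at stake. The single confirmatory test would reject somewhat more often than 5% under the null hypothesis, and the stated 80% power would be somewhat too high. The trial is also meant to support wider use of A-FFIP by other trained professionals, and a standard error without therapist variance describes only the therapists who took part.

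**Working it through.** **Inputs from the protocol article.** Two-sided alpha 5%, power 80%, standardised effect 0.55, 53 evaluable per arm, 20% drop-out and 67 randomised per arm (Sample size calculation). Two therapists per A-FFIP child at four centres, none of them treating EIAU (Setting).

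**Assumed, because not stated.** The number of therapist teams k (8, 16, 24) and the therapist ICC (0.01 to 0.05, with 0.10 as a further case). EIAU children are taken as independent.

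**Is sharing likely?** If no therapist treated more than one child, 67 × 2 = 134 therapists would be needed (somewhat fewer with paired treatment), each trained to the fidelity threshold in the intervention section. Sharing is therefore almost certain, although its extent is unknown.

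**Step 1: the plan's own figure.** The noncentral t distribution gives power 79.3% at 52 per arm and 80.1% at 53, so 53 is right. 53/0.8 = 66.25, rounded up to 67 per arm, 134 in total. The plan's figures reproduce exactly for independent children.

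**Step 2: clustering in one arm.** With m = 53/k children per team and SD 1:

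- Design effect in A-FFIP: DE = 1 + (m − 1) × ICC
- Variance of the difference: (DE + 1)/53, against 2/53 in the plan
- Ratio of true to assumed standard error: r = √((DE + 1)/2)
- True type I error: 2 × (1 − Φ(1.96/r))
- Power: noncentral t with noncentrality 0.55/√((DE + 1)/53), on 104 df, and again on Satterthwaite df with k − 1 for the A-FFIP arm and 52 for EIAU

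Worked example, k = 8 and ICC 0.05: m = 6.625; DE = 1 + 5.625 × 0.05 = 1.281; r = √(2.281/2) = 1.068; type I error = 2 × (1 − Φ(1.835)) = 6.7%; noncentrality = 0.55/√(2.281/53) = 2.65; power 74.7% on 104 df, 71.4% on about 20.5 Satterthwaite df.

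| Teams | ICC | r | Type I error | Power, 104 df | Power, Satterthwaite df |
|---|---|---|---|---|---|
| 8 | 0.01 | 1.014 | 5.3% | 79.0% | 76.3% |
| 8 | 0.02 | 1.028 | 5.7% | 77.9% | 75.1% |
| 8 | 0.05 | 1.068 | 6.7% | 74.7% | 71.4% |
| 8 | 0.10 | 1.132 | 8.3% | 69.8% | 65.7% |
| 16 | 0.01 | 1.006 | 5.1% | 79.6% | 78.7% |
| 16 | 0.02 | 1.011 | 5.3% | 79.2% | 78.2% |
| 16 | 0.05 | 1.029 | 5.7% | 77.9% | 76.8% |
| 16 | 0.10 | 1.056 | 6.4% | 75.7% | 74.5% |
| 24 | 0.01 | 1.003 | 5.1% | 79.9% | 79.4% |
| 24 | 0.02 | 1.006 | 5.1% | 79.6% | 79.1% |
| 24 | 0.05 | 1.015 | 5.4% | 78.9% | 78.4% |
| 24 | 0.10 | 1.030 | 5.7% | 77.8% | 77.2% |

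**Step 3: does the centre term absorb it?** A simulation with four centres and a therapist effect in A-FFIP only was analysed with adjustment for centre (centre indicators standing in for the random effect) and without therapist. Type I error was 5.1% at ICC 0. At ICC 0.05 it was 5.6% with four teams per centre and 6.8% with two; at ICC 0.10, 6.6% and 8.8%. The centre term does not remove the problem.

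**Step 4: covariate gain.** Power returns to its planned level on 104 df if covariates explain a share 1 − 2/(DE + 1) of the outcome variance. At ICC 0.05 this is about 5% (16 teams) to 12% (8 teams); at ICC 0.10, about 10% to 22%.

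**The case against.** The strongest reply is that the effect may be negligible. The protocol sets a fidelity threshold before therapists treat study children, then provides rated session videos, monthly supervision and a yearly workshop, all of which may keep therapist differences small. At ICC 0.01, or with 24 teams, the table shows little change. Baseline BOSCC-AT and age may well win back the lost power. A sensitivity analysis for therapist clustering is also ordinary SAP content, and the article does not say that therapist identity goes unrecorded.

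Most of this stands as a limit on size. It does not remove the point: the primary model is listed in full without therapist, and the 80% figure is stated without its independence condition. Covariates can restore power, but they do not correct a standard error that omits therapist.

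Several stronger readings are tempting, and the document does not support them:

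- That the MMRM treats all children as independent. It models centre and correlation within a child; only therapist clustering is left out.
- That the therapist pool is known to be small, or the standard error known to be wrong. Neither the number of therapists nor the ICC is given.
- That the sponsor expects therapist competence to drive outcome. The Discussion passage is exploratory.
- That EIAU is free of clustering. Group therapy is allowed there, and children may share local providers; this is unknown rather than absent.
- That paired treatment adds a known amount. Its frequency is not given, and the calculation above does not model it.

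**Conclusion.** The concern holds in conditional form. The sample size is correct for independent children. If therapist effects exist in the A-FFIP arm, the planned model leaves them out and the error is in the anti-conservative direction. With 8 to 24 teams and ICC 0.01 to 0.05, the standard error is about 0.3% to 6.8% too small and type I error is about 5.1% to 6.7%. Power is about 80% to 75% (104 df) or 79% to 71% (Satterthwaite df) before covariate gain. At ICC 0.10 type I error is 5.7% to 8.3%, and power falls to between 77.8% and 69.8% (104 df) or 77.2% and 65.7% (Satterthwaite df).

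These figures rest on assumed team numbers and ICCs, equal caseloads, an unclustered EIAU arm, and clean teams standing in for a structure in which each child has two therapists. The distortion is small to moderate, and the remedy is cheap enough to justify acting.

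**What to change.** 1. Make sure that the main therapist or team is recorded for each A-FFIP child.
2. Pre-specify, before unblinding, a partially nested version of the primary MMRM as a sensitivity analysis: a therapist or team random intercept in the A-FFIP arm only, with small-sample degrees of freedom (Kenward-Roger or Satterthwaite). Report it beside the primary result whatever it shows.
3. Add to the sample size section that 80% power assumes no therapist clustering. Give a power range for stated ICC and caseload assumptions, using the degrees of freedom of that model. For 8 to 16 teams and ICC 0.02 to 0.05 this is about 71% to 78%; the 104-df range of 75% to 79% would be too favourable.

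Cost: at most one data field and a few sentences, with no additional patients. The interval in that analysis will be somewhat wider and the stated power slightly less favourable. A single team intercept only approximates care by two therapists, and the A-FFIP-only term leaves any clustering among EIAU providers unmodelled; the report should say both.
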